### Data analysis

Descriptive statistics will be used to report the demographic characteristics of participants in both groups. The baseline characteristics of the two groups will be compared by chi-square or independent t-tests as appropriate. The effectiveness of the intervention will be evaluated by comparing the proportion of younger family members who expressed willingness to encourage their older family members to take up FOBT, as well as their readiness to assist older family members in collecting a stool sample at T1 in both groups. The proportions of older family members who attended medical visit at T2 and reported to have undertaken FOBT at T3 in both groups will also be evaluated. Chi-squared test will be employed for the analysis of these parameters with an intention-to-treat approach. Generalised linear models on the baseline and T1 data will be used to compare the differential changes in two repeated outcome measures for younger family members across the two time points between the two groups, with adjustment for potential confounding variables. The generalised linear modelling will be performed through the Generalised Linear Models Procedure of IBM SPSS statistic v22, depending on the distributions of dependent variables. Descriptive statistics will be used to evaluate dyads’ satisfaction level of the intervention. All statistical tests will be two-sided, with a *p*-value less than 0.05 being considered statistically significant.

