### Randomization

A cluster randomization approach will be utilized in this study. In previous community-based projects, we had identified ten districts in Hong Kong populated with a large number of South Asians. These districts will be randomized into either the intervention or wait-list control group, with five districts allocated to each group respectively. Partner organizations located in each district will be allocated to either group based on the outcome of group allocation of respective districts. Sealed and numbered envelopes will be used during group allocation to ensure concealment. To ensure successful recruitment of 320 dyad participants for the study, we aim to recruit 50–60 dyad participants in each district.

Randomization will be conducted by a research staff member independent from the research team so that outcome assessors and study investigators will be blinded to group allocation. However, owing to the use of a wait-list control group in this study, it will not be possible to blind the dyad participants.

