#### Effectiveness

The ‘Effectiveness’ of the intervention will be assessed by three parameters:First, the research team will evaluate the proportion of dyads with younger family members (aged between 18 and 49) who are willing to encourage their older family members (aged between 50 and 75) to undergo FOBT through family doctors and ready to assist older adults in stool sample collection for FOBT. The level of willingness and readiness will be assessed using an author-developed questionnaire, where younger family members will rate items based on a five-point rating scale. The ratings obtained from intervention and control dyads will be compared subsequently.Second, the research team will also assess the proportion of dyads with older family members (aged between 50 and 75) who have consulted a family doctor for FOBT, completed FOBT and sent their stool samples to the family doctor. A record on the number of older family members of the dyads who have visited family doctor for FOBT will be accessed and the number of stool samples received by the participating family doctors will be recorded. The research team will compare the proportion of participants in the intervention and control dyads who have completed FOBT and provided their stool samples to a family doctor.Third, the research team will assess the intervention dyads’ level of satisfaction of the intervention using an author-developed satisfaction questionnaire with a five-point rating scale.

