### Data collection procedures

Upon receipt of the informed consent, dyad participants will be asked to complete the author-developed questionnaire for the collection of demographic data (T0). At baseline and immediately after the intervention (T1), younger family members of the dyads will be asked to complete the questionnaire that assesses their willingness to encourage older family members to undergo FOBT and their readiness to assist them in collecting stool samples for the test. At T1, dyad participants will also be asked to complete the satisfaction questionnaire to indicate their level of satisfaction of the intervention. A coordinator from our research team will prepare an attendance record, recording the number of older family members of the dyads who attend medical consultation at a family doctor a month post-intervention (T2) and return the stool sample to the family doctor for FOBT 2 months after the medical consultation (T3). Data collection from the dyads in the control group will also be conducted as described above. After project completion, data collectors will approach the persons-in-charge of partner organizations for the completion of a questionnaire enquiring their level of willingness to continue implementing the intervention at their centers.

As a token of appreciation to the dyads’ participation in the intervention, our research team will offer all participants a weighing scale upon completion of baseline data collection.

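### FOBT completion is taken from doctors' records in two sections but from what older members 'reported' in the analysis section, and none of the four effectiveness tests is named primary

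*Protocol article*

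**What the plan says.** Three sections of the protocol article describe the FOBT outcome.

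- **Outcome measures, Effectiveness.** The source is a record: "the number of stool samples received by the participating family doctors will be recorded". The groups are compared on the proportion "who have completed FOBT and provided their stool samples to a family doctor".
- **Data collection procedures.** The source is again a record: "A coordinator from our research team will prepare an attendance record". It counts older members who attend the consultation (T2) and who "return the stool sample to the family doctor for FOBT 2 months after the medical consultation (T3"). Control data are to be collected in the same way. The only participant questionnaires described cover demographics, the younger member's willingness and readiness, and satisfaction; none is given at T3.
- **Data analysis.** The proportion compared is older members who "attended medical visit at T2 and reported to have undertaken FOBT at T3 in both groups".

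On blinding, the Randomization section says that "it will not be possible to blind the dyad participants".

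Data analysis evaluates effectiveness through four proportions: the younger members' willingness to encourage, "as well as their readiness to assist older family members in collecting a stool sample at T1 in both groups", the older members' visit at T2, and FOBT at T3. All four are compared by chi-squared test. The general rule is: "All statistical tests will be two-sided, with a *p*-value less than 0.05 being considered statistically significant". No outcome is called primary. The Sample size estimation section bases 126 dyads per group on a 16.2-point difference in screening uptake, and objective 2 also concerns uptake of screening and FOBT.

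**The concern.** A sample logged as received by a doctor and a test that a participant says was done are different variables. The first does not depend on the participant's account. The second does, and these participants know their group. Intervention dyads will also have just been taught that screening is desirable, so any over-reporting could differ between groups and make the intervention look better than it is.

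The second part concerns which result carries the conclusion. Data analysis puts four outcomes on one footing and presents the younger members' willingness and readiness first. Those two are also the only outcomes given confounder-adjusted models. They are stated intentions, rated immediately after the talk. The trial is sized for uptake, but the document does not say whether uptake means the visit, the returned sample or a reported test. A significant result on intention could therefore be presented as effectiveness when uptake itself shows nothing.

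**Working it through.** **1. The outcome definition, side by side**

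| Section | Event at T3 | Source |
|---|---|---|
| Effectiveness | FOBT completed and sample given to the doctor | Samples received by participating doctors |
| Data collection procedures | Sample returned to the doctor | Coordinator's record |
| Data analysis | FOBT undertaken | What older members reported |

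The first two agree and the third does not. In the Data analysis sentence the older members are the grammatical subject, so self-report is its natural reading.

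**2. Direction of a self-report bias**

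Let p be the true uptake, equal in both groups, and let f_I and f_C be the proportions of unscreened people in the intervention and control groups who nevertheless report a test. The spurious difference is (1 − p)(f_I − f_C), which is positive whenever f_I exceeds f_C. The document gives no value for p, f_I or f_C. With an assumed p of 0.20 and an assumed excess f_I − f_C of 0, 0.05 or 0.10, the result is 0.80 × 0 = 0, 0.80 × 0.05 = 4 or 0.80 × 0.10 = 8 percentage points. This shows the mechanism only and is not an estimate for this trial.

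**3. The plan's own figure**

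Inputs from Sample size estimation: difference d = 0.162, 5% significance, 80% power, 126 per group, 20% attrition; two-sided from Data analysis. The formula for two proportions, without continuity correction, is

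n = [1.960 √(2p̄(1 − p̄)) + 0.842 √(p₁(1 − p₁) + p₂(1 − p₂))]² / d².

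The two uptake rates are not stated, so 126 cannot be confirmed. It results from a control rate of about 22.2–22.5% without continuity correction, or 17.6–17.9% with it. For attrition, 126 / 0.8 = 157.5, which 160 covers. The calculation is for one comparison, of screening uptake, and makes no allowance for three further tests.

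**4. Chance of at least one false positive over four tests**

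- Independent tests, each holding 5%: 1 − 0.95⁴ = 0.185.
- Correlated tests: four equally correlated normal statistics, two-sided 5% limits, 400,000 simulated draws.

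| Assumed correlation | Chance of at least one false positive |
|---|---|
| 0 | 18.5% |
| 0.3 | 17.4% |
| 0.5 | 15.6% |
| 0.8 | 11.4% |

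- One designated test holding 5%: 5%.

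**The case against.** The strongest reply is that the analysis section probably means the recorded event. T3 is defined in Data collection procedures as the return of a sample, with a coordinator's record as its source, and no questionnaire is described at that point. On that reading the word is a slip. This stands to the extent that a reader who infers that the trial will discard its records for self-report goes further than the document allows. The contradiction in wording remains, and whoever runs the analysis should not have to guess.

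A second reply is that a lead outcome is implied, since objective 2 and the sample size both point to uptake. That is fair, and calling the four tests fully equal would be too strong. No sentence says that one significant result of any kind is enough to declare the intervention effective. But the implied lead is never linked to one of the defined outcomes.

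A third reply is that 18.5% overstates the error. It is indeed a ceiling: a returned sample follows a visit, and willingness and readiness come from one questionnaire, so positive correlation is likely. It also presumes that each test holds its 5%, which an individual-level chi-squared test need not do when ten districts are randomised. Naming one primary outcome does not cure that separate problem.

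Finally, multiplicity rules are often left to an analysis plan, and a primary outcome may be named in a registry entry or full protocol not at hand. The absence of a multiplicity rule is therefore not the point. The point is that this document sets the trial's size on one outcome and then fixes an analysis that does not identify it and defines it inconsistently.

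**Conclusion.** The point holds as an inconsistency that should be corrected. That the FOBT outcome has two incompatible sources is certain from the text. That the results would be biased is conditional: it requires the analysis section to be followed literally and over-reporting to be more frequent in the intervention group. The document supports the direction of such a bias as plausible but gives no basis for its size.

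That no outcome is named primary is also plain. If any of the four tests were allowed to support the conclusion, the chance of at least one false positive would be at most 18.5% under independence, and about 11–17% at assumed correlations of 0.8 to 0.3, instead of 5%. These figures assume that each test holds its nominal level.

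A reader might infer that the trial has abandoned objective ascertainment, or that its actual error rate is 18.5%. The document supports neither.

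**What to change.** 1. In Data analysis, replace the reported-FOBT wording with: *stool sample recorded as received by the family doctor by T3*. Use the same definition in Effectiveness and Data collection procedures.
2. State that it is determined in the same way and over the same time window in both groups. T2 is timed from the intervention, which controls receive only after post-intervention data collection, so the starting date for controls needs to be stated.
3. Put all enrolled dyads in the denominator. Districts are randomised and dyads are recruited within them, so enrolled describes the set better than randomised.
4. Name this as the single primary outcome, and say in Sample size estimation that it is the uptake to which the 16.2 points and 126 dyads per group refer. Label willingness, readiness and visit attendance as secondary.
5. If self-reported tests or tests done elsewhere are collected, include them in a sensitivity analysis only.

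**Cost.** The change is mainly one of wording, because the records are already planned. The real drawback is that tests done with non-participating doctors are not counted. If this happens more often among controls, the recorded outcome would itself favour the intervention, and the sensitivity analysis is there to show it. Collecting those outside tests would be extra work if it is not already intended.

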### Design

This study will utilize a cluster randomized controlled trial design, which includes a wait-list control group.

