### Sample size estimation

Sample size calculation of this study is based on the findings of a previous study on the implementation of an intervention aiming to enhance CRC screening uptake among African Americans, under which the difference in CRC screening uptake between the intervention and control groups at six-month follow up was compared [29]. The authors observed a difference of 16.2% in the proportion of intervention and control participants who had undergone screening. To reject the null hypothesis that no difference in screening uptake exists between the two groups at a 5% level of significance, both groups require 126 dyads to achieve a power of 80%. To reach an attrition rate of 20%, a total of 320 dyads shall be recruited, with 160 dyads in each group.

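### The chi-squared tests treat dyads as independent although only ten districts are randomised, so the type I error exceeds 5% for any positive intracluster correlation

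*Protocol article*

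**What the plan says.** The Design section states: "This study will utilize a cluster randomized controlled trial design, which includes a wait-list control group". Randomization names the unit: "These districts will be randomized into either the intervention or wait-list control group, with five districts allocated to each group respectively". Partner organisations take the arm of their district.

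Data analysis then names the test. For the younger members, the proportions willing to encourage FOBT and ready to assist are compared at T1. The older members' outcomes are introduced with the words "The proportions of older family members who attended medical visit at T2 and reported to have undertaken FOBT at T3 in both groups will also", which again sets up a comparison of the two arms. The next sentence covers all of these: "Chi-squared test will be employed for the analysis of these parameters with an intention-to-treat approach".

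A second method is given for the younger members only: "Generalised linear models on the baseline and T1 data will be used to compare the differential changes in two repeated outcome measures", with adjustment for confounders that are not listed. The Abstract mentions only the generalised linear models procedure, but Data analysis confines it to the younger members' ratings. The FOBT and visit comparisons therefore rest on the chi-squared test alone.

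On error rates, "All statistical tests will be two-sided", and the sample size is set "at a 5% level of significance". Sample size estimation states that "both groups require 126 dyads to achieve a power of 80" per cent. No ICC, design effect, random effect, GEE, robust variance or district-level analysis appears anywhere in the article.

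**The concern.** An ordinary chi-squared test takes its variance from the number of dyads, as if each had been allocated separately. Here there are ten allocations. Dyads in a district share the health talk at a partner organisation, the organisation's engagement, the representative who accompanies willing dyads, and the local family doctors who agreed to take part. All of these can move FOBT uptake for a whole district at once. With five districts per arm, such differences do not average out reliably, and the test has no term for them.

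The error is in the anti-conservative direction: chance differences between districts can be reported as an intervention effect. FOBT uptake is the behaviour named in the effectiveness objective and the outcome on which the sample size is based. The results are also meant to inform whether the intervention enters existing support services.

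**Working it through.** **Inputs.** From the article: 10 districts, 5 per arm; two-sided 5% level; 126 dyads per group needed; 320 recruited (160 per group); 20% attrition; a 16.2-point difference; and, under Randomization, 50–60 dyads per district. Assumed, because the article gives neither: the ICC and the control-group uptake.

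**The plan's own figure.** The attrition step reproduces: 126/0.8 = 157.5, so 158 per group and 316 in total, rounded to 320. The 126 cannot be checked uniquely, because no base rates are given. The usual two-sided formula for two proportions gives 126 at control rates of about 22.2–22.5% without continuity correction, or 17.6–17.9% with it (or the mirror-image high rates). This is an individual-level formula with no design effect.

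**Dyads per district (m).** Analysed: 126/5 = 25.2. Recruited: 320/10 = 32. Under the recruitment aim in Randomization: 50 to 60, which implies 500–600 dyads and does not agree with 320.

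**Type I error of the chi-squared test.** The design effect is DE = 1 + (m − 1) × ICC. The test statistic is too large by √DE, so the actual error is 2 × [1 − Φ(1.96/√DE)].

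Example, m = 25.2 and ICC 0.01: DE = 1 + 24.2 × 0.01 = 1.242; 1.96/√1.242 = 1.759; error = 7.9%.

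| ICC (assumed) | m = 25.2 | m = 32 | m = 50 | m = 60 |
|---|---|---|---|---|
| 0 | 5.0% | 5.0% | 5.0% | 5.0% |
| 0.005 | 6.4% | 6.8% | 7.9% | 8.5% |
| 0.01 | 7.9% | 8.7% | 10.8% | 12.0% |
| 0.02 | 10.8% | 12.4% | 16.4% | 18.4% |
| 0.05 | 18.7% | 22.0% | 29.1% | 32.4% |

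**Check by simulation.** Beta-binomial data were generated with no intervention effect, 5 v 5 districts of equal size, uptake 10%, 20% or 30%, and 200,000 replicates per setting. For ICC 0.01 to 0.05 the chi-squared test rejected in 7.6–18.8% of trials at m = 25 and 8.6–22.4% at m = 32. A t-test on the ten district proportions (8 df) rejected in 4.6–5.2% in every setting, including ICC 0.

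**Power of a valid analysis.** Assume a control rate of 22.4%, where the formula gives 126 per group, and 38.6% under intervention. With m = 25 the standard error of the difference is √{DE × [0.224 × 0.776 + 0.386 × 0.614]/(5 × 25)}, which is 0.0573 at ICC 0. The noncentrality is 0.162/0.0573 = 2.83 on 8 df, giving power of 69–70%. The same calculation gives about 61% at ICC 0.01, 53% at 0.02 and 38–39% at 0.05.

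**The case against.** The strongest defence is that the size of the error is unknown. The article gives no ICC; at ICC 0 the chi-squared test keeps its 5%, and at 0.005 the excess is small. That stands as a limit on the size. A reader might infer that 8–22% is the trial's true error rate. The documents do not support that, since both ends depend on an assumed ICC and on which of the article's district sizes is used. The direction does not depend on these assumptions.

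A second defence is that an analysis plan not shown may handle clustering. That would answer an omission, but the article does not leave the method open: it names a test that does not fit its design. The intention-to-treat wording does not help either, because it settles who is analysed and not how the variance is formed.

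A reader might also infer that the generalised linear model enters a younger member's baseline and T1 ratings as if they came from two people. The text does not say so. It calls the outcomes repeated, compares changes, and gives no covariance structure, a detail commonly left to an analysis plan. Nor can district be said to be excluded from that model, since the adjustment variables are not listed. It is simply not named. Finally, Data analysis plans tests and p-values and mentions no confidence intervals, so there is no planned interval to criticise.

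**Conclusion.** The point holds for the chi-squared comparisons of T1 willingness and readiness, the T2 visit and T3 FOBT. The stated test contradicts the stated randomisation, and its type I error is above 5% for any positive ICC. With 25 to 32 dyads per district and an assumed ICC of 0.01 to 0.05, the error is about 8–22%; with 50–60 dyads per district it is about 11–32%. These ranges are illustrative and assume equal district sizes. Because FOBT uptake rests on this test alone, this should be corrected before analysis.

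**What to change.** In Data analysis, replace the chi-squared tests with one pre-specified analysis that respects the randomised unit. Any of these would serve:

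- a t-test on the ten district proportions, with 8 df;
- an exact permutation test over the 10!/(5! × 5!) = 252 possible allocations;
- a logistic mixed model or GEE with district as the cluster and a small-sample correction for ten clusters.

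Name district as the cluster level in the generalised linear models for the younger members as well, and report the ICC.

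The cost is one reworded paragraph, slightly more analysis work and less favourable p-values, with no new data. It also affects Sample size estimation. The 126 per group carries no design effect, so a valid analysis has less power than stated. The 80% should be restated with an explicit control rate, ICC and district size. The power loss shown above depends on the assumed control rate near 22%. At a 10% control rate, for example, 126 per group would have about 92% power before any allowance for clustering, so the loss would start from a higher level.

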### Ethical considerations

Ethical approval has been obtained from the Ethics Committee of the authors’ study institution. Prior to the enrollment of dyad participants, our research team will provide detailed information of the study via an information sheet to explain the aims and detailed procedures of the study. Potential dyad participants will be informed of their rights to withdraw from the study at any stage without penalty. They will be assured of anonymity and confidentiality of any data they provide throughout the study, through the use of participant numbers and the storage of sensitive data in locked cabinets. Dyads will be enrolled into the study only after they have provided their written informed consent to our research staff.

